### **10.1.2.2. PET scan**

The PET data collected will include:

- An early acquisition in PET-Amyvid®, allowing a measurement of cerebral perfusion;
- A late acquisition in PET-Amyvid®, allowing a measurement of the binding of the marker to amyloid deposits;
- A PET-F-FDG acquisition, allowing a measurement of the cerebral metabolism.

These acquisitions will all be collected on a high spatial resolution camera. An attenuation correction will be made from an estimate of the attenuation map by X-ray scanner acquired with a low dose protocol. The resulting images will be collected in electronic format to be pre-processed and processed with brain imaging software.

### **10.1.2.3. Blood sample on V1**

Numerical results of the various marker assays from the V1 blood sample (see Section 7.3.4, Table 8) will be collected from all participants.

GWAS and APOE genotyping will be collected for all participants who have signed the specific consent; these results will be communicated to the investigators via the neurologist in charge of the project.

### **10.1.2.4. Neuropsychological and behavioural assessment on V1**

The neuropsychological data collected during the V1 neuropsychological and behavioural assessment correspond to the various neuropsychological test scores (see section 6.7, table 5). They correspond to scores, most of the time numerical, single or multiple depending on the tests with:

- responses times
- and/or the number of correct answers
- and/or the number of errors
- with total scores and sub-scores

### 10.1.2.5. Assessment of wakefulness and sleep

The assessment of wakefulness and sleep will include the collection of

- Scores on various wakefulness and sleep questionnaires;
- Actimetry measurements: this is a continuous recording of the activity-rest rhythm. This recording makes it possible to calculate a fragmentation index of the activity-rest rhythm;
- Polysomnographic recordings: this is an EEG recording during wakefulness and two nights of sleep. It allows us to collect different information on the reactivity of the brain during the presentation of auditory stimuli, the spectral profile and the functional connectivity during the awake state. For the sleep recordings, we will collect in particular the sleep latency, the sleep efficiency (time spent sleeping / time spent in bed), the sleep duration, the number of nocturnal awakenings, the percentage and the time spent in each sleep stage;
- With the Somno-Art® device: total sleep time, sleep efficiency, sleep latency, WASO (wake after sleep onset), quantities of different sleep stages, number of cycles, number of awakenings, number of transitions between stages and sleep instability index;
- With the consolidation task: the rate of improvement or forgetting during the night.

### 10.1.3. Data collected during the intervention

During the intervention, information will be collected on the participants' diary, including the duration of the daily exercises, the evaluation of their difficulty, etc. (numerical and qualitative data), the therapeutic alliance between the participant and the teacher, and the quality of the social ties forged in the group and between the participant and their partner during the intervention.

When the subject fills in his daily questionnaire on the iPad, the data are retrieved in coded and pseudo-anonymized text format on his tablet. The data is never transmitted via the Internet. The functionalities of the iPad which are not used for the trial are deactivated (Internet, etc.). Restrictions are put in place for access to the Internet browser and the "App store" from Apple tablets. To do this, the following procedure will be applied: General/restriction/activate restrictions/enter a code. The access codes to change these settings will not be known to the participants. They will therefore have no way of downloading new applications or surfing the Internet via these tablets and consequently the data collected will not be transmitted via the Internet. To connect to their tablet, participants must enter a code that is at least 7 characters long, including at least one special character or letter. The validity period is less than 12 months. The number of unsuccessful attempts is 3 before the account is blocked. Participants must then bring their tablet to the IT staff in charge so that they can restore access. This application has been developed by a certified staff: [name] is a study engineer (IE2) at INSERM in the Centre de Recherche en Neurosciences de Lyon, in the DYCOG team, INSERM U1028 - CNRS UMR5292 ([contact]). [name] is also a certified developer at Apple. Once a month, the English and meditation intervention subjects bring their tablets to class to be processed by a computer scientist from the English and meditation workpackage team, respectively.

The data is then downloaded to a computer exclusively for this purpose and the data is deleted from the tablets. Throughout this process, the data remains pseudo-anonymized. During the transfer of the data, the new teaching material used in the interventions is downloaded to the participant's tablet. The data, once decoded by a computer expert, will then be transmitted to the data management structure via a secure file transfer platform and attached to the global database in order to analyze them in relation to the other modalities.

#### **10.1.4. Data collected at the 9-month follow-up visit (V2)**

The neuropsychological data collected during the V2 neuropsychological and behavioural assessment correspond to the various neuropsychological test scores (see section 6.7, table 5). They correspond to scores, most of the time numerical, single or multiple depending on the tests with:

- response times
- and/or the number of correct answers
- and/or the number of errors
- with total scores and sub-scores

#### **10.1.5. Data Collected at the 18-Month End-of-Intervention Visit (V3)**

The data collected at the 18-month follow-up visit (V3) will be similar to that collected at the inclusion visit (V1). This visit will include, in addition to these examinations, a semi-structured interview about the experience of English learning and meditation during their participation in the Age-Well trial. The qualitative data from this dictaphone-recorded interview will then be transcribed in full. A classical content analysis will then be performed (manual processing and/or use of software). This qualitative interview will only concern participants who have attended an intervention.

The qualitative data from the interview with the meditation and English teachers after the end of the interventions will be recorded with a dictaphone and then transcribed in full. A classical content analysis will be performed.

### ***10.2. Data collected at the 29±6 month post-procedure follow-up visit (V4)***

The neuropsychological data collected during the V4 neuropsychological and behavioural assessment correspond to the various neuropsychological test scores (see section 6.7, table 5). They correspond to scores, most of the time numerical, single or multiple depending on the tests with:

- response times
- and/or the number of correct answers
- and/or the number of errors
- with total scores and sub-scores

**This visit will include the same examinations as in the V1 inclusion visit and in the V3 post-intervention follow-up visit except for the PET-Amyvid examination and the overnight polysomnography.**

### **Anthropometric data**

In order to improve the quality of anthropometric measurements (height, weight, BMI, abdominal girth and hip circumference), the acquisition of a body composition scale (Tanita MC-580) was made to allow accurate measurement of: Weight (kg), fat (%), body fat (kg), lean body mass (kg), hydration rate (kg), muscle mass (kg), bone mass (kg), impedance (Ohm), basal metabolic rate (kJ; kcal), visceral fat (level) and metabolic age (year), as well as BMI, Sarcopenic Index (SMI; kg/m^2) and Skeletal Muscle Mass (SMM; kg and %).

### **The CIRS score (Cumulative Illness Rating Scale)**

The CIRS score is calculated from medical (history, treatments), biological (Body Mass Index (BMI), Blood Pressure (BP), Blood Count (CBC), Lipid Abnormality Investigation (LAI), Fasting Blood Glucose), neuropsychological (Mini-Mental State (MMS)), and the Apnea-hypopnea index (AHI) score from polysomnography, collected at visits 1, 3, and 4 entered in the eCRF. It provides a global numerical measure of all the pathologies of an individual.

## **10.3. Definition of source data**

Source data are all the information contained in original documents, or in authenticated copies of these documents, which relate to clinical examinations, observations or other activities carried out in the framework of biomedical research and which are necessary for the reconstruction and evaluation of the research. The documents in which the source data are recorded are called source documents, regardless of the medium used (paper, electronic...).

## **10.4. Data circuit before computer entry**

Regarding the consistency check of the collected data, they are retrieved once a month for each participant in the English group and the meditation group. On this occasion, we can verify that the tablet is working as intended. In addition, we record the participants' data via the Kallysta case and the Dapi software installed on a MacBook computer that is not connected to the internet or any intranet and is password protected. We then check that the participants fill in the questionnaire according to our expectations (once a day). This is the first method that allows us to know that the use of the tablets by the participants is consistent with our expectations. The second method we use goes into a little more detail about the data recorded. In particular, we track practice time by verifying that, on the day of the weekly course, participation is around 2 hours on average for the participants. We can then confirm that participants are filling out their tablets as we explained to them. If this is not the case for a participant, we can re-explain the instructions for correctly filling out the questionnaire on the tablet.

As for the maintenance of the equipment, tablets, computers and briefcases, this is carried out by the computer specialists of the center where the equipment is located: the computer specialists of the Carré international for the equipment attached to the English learning intervention and the Cyceron center for the equipment attached to the meditation intervention. In both cases, the equipment is stored in locked cabinets, in locked rooms. In addition, to enter these buildings, it is necessary to use a biometric code to gain access.

Concerning the traceability of the data, they are recovered by wire from the tablet and without the need for an internet network. The saved file has the date of recording and data collection.

These data files collected via the tablets will then be decrypted and formatted at Cyceron by a member of [name]'s team and transferred to an Excel spreadsheet. This Excel table will then be sent in a secure way to the data management team who will keep this file for later availability with the database from the eCRF, the anonymization code being the element that allows to match the collected data to the right participant.

Data will be collected by the referents and investigators throughout the protocol. The information collected will be kept in the source file and the scores/information collected will be entered into the e-CRF by the referents and investigators.

The imaging data will be acquired on the Cyceron Center's imaging equipment and transferred in electronic format via the Center's internal network to the protocol investigators. The volume and perfusion of the anterior cingulate cortex and insula will be obtained after transformation of the data via SPM and/or Freesurfer and extracted to be entered into the eCRF.

For biological data, blood samples will be sent directly from the CRC of the Caen University Hospital to the different research laboratories in charge of the analyses (see section 7.3). Once the results of the different analyses have been received at the CRC, the data will be sent pseudo-anonymized with the participant code of the trial to the Inserm referent for entry into the eCRF.

Cognitive data will be collected directly in paper and electronic format and scored by the referent and/or neuropsychologist.

Finally, actimetry and polysomnography data will be directly retrieved in electronic format by the investigators.

## **10.5. Computerized data entry**

Until December 31, 2020, the eCRF and database are the responsibility of EUCLID. After this date, the frozen database with data from inclusion to the end of intervention visit (V3) will be transferred to and under the responsibility of the IT department of the Cyceron Center in Caen. The Cyceron Center, through the MMA funding, will call upon the easyCRF service provider who will develop the part of the eCRF corresponding to the data collected during the follow-up visit at 29 months post-intervention (V4), the inclusion visit of the experts (V1) and who will consolidate the database and ensure its security.

## **Software used**

EUCLID: The software used for data management is Ennov Clinical, from Ennov, in its version 7.0 or any later version. This software has been developed by Ennov-Clinical in compliance with the FDA Guidance for Computerized System Used in Clinical Trials, electronic signature and audit trail (21CFR Part 11) as well as international standards (CDISC, ICH, GCP 2001/20/EC...).

easyCRF: The software used for data management is Easy-CRF, from the company Easy-CRF, in its version 6.2.0 or any later version. This software has been developed by Easy-CRF in compliance with the FDA's Guidance for Computerized Systems Used in Clinical Trials (2007), electronic signature and audit trail (21CFR Part 11) as well as ICH, GCP 2001/20/EC.

## **Data hosting**

EUCLID: Ennov-Clinsight ensures the storage and maintenance of the database in accordance with the specifications defined in detail in the Ennov Clinical Supplier CDC and Ennov-Clinsight procedures. OVH hosts the server in a data center located in Roubaix (59), France.

easyCRF: The company Easy-CRF ensures the storage and the maintenance of the database according to its own procedures (backup, restoration, disaster recovery plan, change management). The company AZNetwork hosts the server in a data center located in France in Alencon (61).

## **Data safety**

EUCLID: Ennov-Clinsight ensures the security of the hosted database. The local server is located in Strasbourg, France and an external backup server is located in Gravelines. According to the rules described in the standard operating procedure, the management of access rights is the responsibility of the EUCLID CS administrator and the management of access to the eCRF for investigators and their collaborators is the responsibility of the EUCLID ARC.

easyCRF: Easy-CRF has implemented a certain number of logical measures to ensure the security of the data located on its server (firewall, antivirus, rootkit detection, intrusion detection). The physical protection measures are implemented by AZNetwork in accordance with the specifications for hosting health data. A login/password access is associated to each user. The rights of each user are configured according to their profile (promoter, investigator, CRA, etc.) and their auditable values. A trace of connections, accesses to the different pages of the eCRF, and registrations is kept for the entire duration of the study's operation.

## **Data entry**

Trial data should be entered by the investigator or delegate, who should date and sign the eCRF. If the investigator delegates and authorizes other staff members to make entries in the eCRF, their names, functions, signatures and initials must be documented in writing (e.g., Center Delegation Form). The eCRF must be completed during/after each trial visit.

All individuals responsible for entering data into the eCRF must be trained and designated to perform this task.

Access to the eCRF for data entry or review will require a separate individual access code assigned only to center staff members who will be entering trial data and to members involved in trial monitoring who may be reviewing trial data. Data are collected in the eCRF, to which the sponsor and monitor have "read only" access.

### **Database archiving**

The archiving of the database is the responsibility of the sponsor.

## **10.6. *Description of data processing, verification and validation methods (data management)***

### **10.6.1. Processing of eCRF data**

#### **Data validation**

Consistency tests are scheduled by the data manager to check the consistency and the data entry in the eCRF. The list of consistency tests is predefined by the trial project team, then transmitted to the data manager who writes the validation plan for the data.

The management of correction requests is done by the data manager in due time. Additional correction requests can also be made by the sponsor's CRA. Correction requests are sent to the investigating center via the eCRF. The investigators respond directly in the eCRF.

#### **Data coding**

Treatment and clinical events are coded in the eCRF by the sponsoring ARC to monitor and analyze the data.

The following dictionaries are used to code medical verbatims:

- ▲ MedDRA: *version 18.1, for the coding of pathologies*
- ▲ WHODRUG: *June 2016 version, for treatment coding*

#### **Database freeze**

The database must be frozen in order to perform the final analysis. A review of the data is performed before the database is frozen by the entire project team in charge of the trial.

#### **Data transfer**

Data transfers (sending, receiving) are carried out in accordance with the procedure in force. The data transfer procedures must be defined in the Data Management Plan. For security reasons, data files are pseudo-anonymized and then transferred via a secure platform.

## 10.6.2. Preprocessing of the imaging data

### Anatomical MRI data

- **MRI-T1.** The data will be pre-processed in order to i) isolate the voxels (3D pixels) corresponding to the cerebral grey matter, and ii) to "normalize" the brains (deform them so that they are superimposable and therefore comparable between individuals) via the SPM12 software (Statistical Parametric Mapping; Wellcome Dept of Cognitive Neurology, London, UK). These data will then be used to obtain indices of cortical volume or thickness. In addition, T1-MRI data will be used as a "support" for the analysis of most other imaging modalities (fMRI, DKI, PET...).

Among others, volume values of the anterior cingulate cortex and insula will be extracted from the pre-processed MRI images ("region of interest" analysis) in order to perform the analyses to address the primary evaluation criterion.

- **MRI-FLAIR.** The data will be preprocessed to extract the volume, number and location of white matter hyperintensities using WHASA software (Samaille et al., Plos One 2012).
- **MRI-T2-HCP.** These high-resolution hippocampal-targeted images will allow for segmenting, and thus calculating the volume of hippocampal subfields, both by manual tracing following a protocol developed (La Joie et al., Neuroimage 2010) and used (La Joie et al., Neuroimage Clinical 2013; de Flores et al., HBM 2015) in the laboratory and an automated procedure via ASHS software (Yushkevich et al., HBM 2015).
- **MRI-DKI.** Diffusion imaging data (DKI) will allow, after data processing with FSL (Jenkinson et al., Neuroimage 2012), ACID (SPM Toolbox; Mohammadi, 2010) and DKE (Jensen et al., NMR Biomed 2010; Tabesh et al., Magn Reson 2011), to reconstruct axonal fiber bundles and calculate diffusion and "kurtosis" parameters within the white matter. These data will thus provide clues to the structural connectivity.
- **MRI-QSM.** Magnetic susceptibility imaging data will be processed using imaging software. The magnetization vector phase information will be used in the form of a mask applied to the magnitude images to enhance the contrast and thus highlight susceptibility differences between tissues (Acosta-Cabronero, 2013).
- **MRI-ASL.** The perfusion imaging data will be processed with imaging software. These data will allow after processing to calculate an index of cerebral blood perfusion.
- **MRI-HR-DTI-Locus.** High-resolution imaging data will be processed with imaging software to better assess the links between hippocampal subregions and locus coeruleus.

The processing of these acquisitions with imaging software will thus allow to obtain cerebral "maps" or average values extracted in certain regions (analysis in regions of interest) which will allow to analyze the cerebral anatomy of all participants with the help of different indices: density/volume of grey and white matter, cortical thickness, hippocampal subfields, white matter bundles, magnetic susceptibility of tissues... and compare brain anatomy between groups or within the same group before and after the intervention.

### **Functional MRI data (at rest and in activation)**

The different steps of pre-processing of the fMRI images will be performed with the SPM12 software. This procedure includes the realignment of the different volumes acquired: correction of movements during the functional acquisition (realignment of the different functional volumes on the first functional volume acquired), correction of the temporal shift ("Slice Timing" function of the SPM12 software), realignment of the functional images on the corresponding T1-MRI, spatial normalization and data filtering (see Villain et al., 2010).

- **fMRI at rest:** Co-variance maps (ICA maps) and functional connectivity maps for each participant (first level analyses) will be made.
- **Activation fMRI:** the variations of the BOLD signal amplitude in the different experimental conditions will be modeled in a first level analysis in each participant in order to reflect in each participant the neural activity specific to a particular cognitive activity (= activity specific to an experimental condition).

The imaging treatments will thus allow to have activation "maps" for each acquisition. The average activity over the whole sequence will be evaluated for the sequences at rest and can thus be compared between groups or within groups before and after intervention. For the activation sequences, the neuronal activity in the different experimental conditions will be isolated in order to be able to compare the cerebral substrates of each of them, between the groups and before versus after intervention.

### **PET data**

PET data will initially be corrected for partial volume effects using a three-compartment method (Giovacchini et al., J Nucl Med 2004), implemented in the 'PMOD' software (PMOD Technologies Ltd., Adliswil, Switzerland) and already used in the study of older adults in the laboratory (La Joie et al., J Neurosci 2012; Besson et al., J Neurosci 2015). The remaining pre-processing operations will be performed using SPM12 software. The corrected PET data will first be realigned to the corresponding anatomical MRI images. The spatial normalization of the PET images will be optimized by applying the normalization parameters of the corresponding T1-MRI. The PET data will then be quantitatively normalized individually by dividing each value by the average value of a so-called "reference" region (e.g. cerebellum, white matter) determined by the corresponding T1-MRI and an anatomical atlas (Tzourio-Mazoyer et al., Neuroimage 2002); the final image will thus be a Standardized Uptake Value Ratio (SUVR). The reference region may vary according to the analyses and will be chosen because of its preservation in terms of beta-amyloid deposits, tau pathology and hypoperfusion.

- **PET-Amyvid® early-frame.** Data acquired within 10 min after tracer injection will be preprocessed as described by Hsiao et al (EurJNuclMedMolImaging 2012) to create brain perfusion maps that will be analyzed in the whole brain (voxel-to-voxel analysis via SPM12) or by an analysis method in regions of interest.

In addition, volume values of the anterior cingulate cortex and insula will be extracted from the pre-processed MRI images ("region of interest" analysis) to perform the analyses to address the primary evaluation criterion.

- **PET-Amyvid® late-frame.** The data acquired within 50 min after tracer injection will be preprocessed to create maps of amyloid deposition labeling that will be analyzed in the whole brain (voxel-to-voxel analysis via SPM12) or by an analysis method in regions of interest. Furthermore, the preprocessed data will allow to obtain a global cortical labeling value after extraction of the average SUVR value in a mask previously developed in the laboratory (Besson et al., J Neurosci 2015) in order to interrogate regions particularly susceptible to beta-amyloid deposits.
- **PET-F-FDG.** Data acquired within 50 min after tracer injection will be preprocessed to create maps of radiolabeled glucose labeling that will be analyzed in the whole brain (voxel-to-voxel analysis via SPM12) as well as by a method of analysis in regions of interest corresponding to the most affected regions in AD (the posterior cingulate and temporo-parietal cortex; Besson et al., J Neurosci 2015).

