### 11.2. *Calculation of the study size*

#### Study on non-expert seniors:

The comparison between the meditation group and the no-intervention group is going to focus on the difference in 1) volume and 2) perfusion of the anterior cingulate cortex 18 months after the start of the intervention compared to the value at inclusion, with an expected effect size of 0.75 (effect size of short-term meditation vs. no intervention, from a meta-analysis on the effects of meditation on brain imaging markers: Fox et al, 2014). Given that the intervention in the current protocol is 18 months, we consider that the effect size will be at least equal to 0.75.

The same effect size of 0.75 is expected for the comparison between the meditation group and the English learning group on the difference in 1) insula volume and 2) insula perfusion 18 months after the start of the intervention compared with the inclusion value.

To show an effect size of 0.75 for each comparison, with 80% power and a two-sided first-species risk of 1.25% (Bonferroni correction because four comparisons will be performed) 42 participants per group must be recruited for a total of 126 participants.

Assuming that the effect size assumptions are conservative and that precautions are taken at the time of recruitment to best ensure adherence of participants to the trial, we expect that the risk of dropout after knowledge of the randomization group is very low and that the power of the study is preserved. However, we will implement close monitoring of these refusals at the beginning of the trial. In order to increase the statistical power of the secondary analysis on the FDG-PET examination carried out from

the second wave of inclusion, 24 participants will be recruited in addition, i.e. 8 additional participants per group (meditation, English, passive control) for a total of 150 participants.

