## STATISTICAL ANALYSIS PLAN

- brain functional connectivity measures in all brain voxels at rest in a non-meditative state ;
- Brain amyloid load (of the PET-Amyvid® radiotracer) measured in all brain voxels as well as in a global grey matter mask;
- Brain glucose uptake at rest;
- Brain activity measured with fMRI specifically associated with emotional processes (comparing emotional to neutral items) during the Rest-SoVT task.
- Brain activity measured with fMRI specifically associated with attentional processes (alertness, inhibition, sustained attention) during the AX-CPT task.

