## Sample size

### **For the randomized clinical trial with non-expert seniors:**

The comparison of the meditation vs. no intervention arms will focus on the change in 1) volume and 2) metabolism of the anterior cingulate cortex from baseline to the end of the 18-months intervention, with an expected effect size of 0.75.

We expect the same effect size of 0.75 for the comparison between the meditation arm and learning of English arm on the change in 1) volume and 2) metabolism of the insula from baseline to the end of the 18-months intervention.

To demonstrate an effect size of 0.75 for each of the four comparisons, with 80% power and a two-sided type I error of 1.25% (Bonferroni correction for test multiplicity), 42 participants per arm need to be included for a total of 126 participants.

In order to increase the statistical power of the secondary analysis on the PET-FDG examination carried out starting from the second wave of inclusion, 24 additional participants will be recruited (additional 8 participants per group) for a total of 150 participants.

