#### **Radiological outcomes (OBJECTIVES 2, 4, 6, 7 and 8):**

- Grey and white matter volume in all brain voxels;
- hippocampal and hippocampal subfield volumes;
- Brain perfusion in all brain voxels;
- Fractional anisotropy and mean diffusivity in all brain voxels;
- number, size, type and location of white matter lesions;
- magnetic susceptibility index in all brain voxels;
- brain functional connectivity measures in all brain voxels at rest in a non-meditative state ;
- Brain amyloid load (of the PET-Amyvid® radiotracer) measured in all brain voxels as well as in a global grey matter mask;

- Brain activity measured with fMRI specifically associated with emotional processes (comparing emotional to neutral items) during the Rest-SoVT task.
- Brain activity measured with fMRI specifically associated with attentional processes (alertness, inhibition, sustained attention) during the AX-CPT task.

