**Objective 8 (WP 6)**

Comparison and correlations between FDG-PET measurement and early PET-Amyvid® perfusion measurement to better understand the links (and possible modifications of coupling) between metabolism and perfusion and compare the sensitivity of the two measures to assess the effects of the interventions.

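### FDG-PET, the stated reason for 24 extra participants, is missing from the secondary SAP's outcome list, and Objective 8 fixes no common region, population or metric for comparing FDG with early-Amyvid perfusion

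*Combined protocol and SAP*

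**What the plan says.** **Sample size.** Protocol section 11.2 bases the trial on the primary comparisons: "42 participants per group must be recruited for a total of 126 participants". It then adds more for FDG: "24 participants will be recruited in addition, i.e. 8 additional participants per group (meditation, English, passive control) for a total of 150 participants". The secondary SAP's Sample size section gives the same reason: "In order to increase the statistical power of the secondary analysis on the PET-FDG examination carried out starting from the second wave of inclusion". No FDG effect size, alpha or target power is stated.

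**Outcome lists.** Protocol section 5.2 lists resting glucose consumption among the imaging measurements, under a heading that covers Objectives 2 and 8. The primary SAP (section 1.7.2) lists "Brain glucose uptake at rest". The secondary SAP's list, headed "Radiological outcomes (OBJECTIVES 2, 4, 6, 7 and 8"), goes from amyloid load to the two task-fMRI outcomes with no FDG line between them.

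**Regions.** Protocol section 10.6.2 plans a voxel-wise whole-brain FDG analysis and, beside it, an analysis in "regions of interest corresponding to the most affected regions in AD (the posterior cingulate and temporo-parietal cortex"). The primary perfusion outcomes in section 5.1 are in the anterior cingulate and insula. The FDG pilot described in section 1.2.3.2 reported its differences in those two regions.

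**Objective 8.** The secondary SAP plans comparisons and correlations between the two PET measures, in order to "compare the sensitivity of the two measures to assess the effects of the interventions". It says no more about method.

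**Missing data.** Under Definition of analysis populations, the secondary SAP's intention-to-treat analysis replaces any missing value by failure. Its conventions for missing data treat unknown, not done and not applicable alike.

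**The concern.** The one analysis that justified a larger trial has no entry in the outcome list of the document that governs it. No FDG endpoint is named in the regions where the trial expects an effect.

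Objective 8 is open in three further ways. The regions compared can be chosen after the results are seen. The tracers can be compared in different numbers of people, because FDG began a wave later. And the default missing-data rule, taken at its word, fills in a worst-case FDG change for people who were never scheduled for a baseline FDG scan. A correlation between tracers does not by itself measure sensitivity to an intervention, so the statement about sensitivity must rest on a comparison that the plan leaves undefined. A conclusion that one tracer is more sensitive could then reflect region, sample size or imputation as much as biology.

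**Working it through.** **1. The plan's own figure.** Section 11.2: "To show an effect size of 0.75 for each comparison, with 80% power and a two-sided first-species risk of 1.25"%. The exact two-sample t calculation gives 41.24, so 42 per group, with power 80.9%. The normal approximation gives 40. The stated 42 is reproduced.

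**2. Who can have FDG.** Protocol sections 6.6 and 6.7 give waves of 42, 54 and 54, and allocation is 1:1:1.
- All waves: 42 + 54 + 54 = 150, or 50 per arm.
- Waves 2 and 3: 54 + 54 = 108, or 108/3 = 36 per arm.
- Wave 1: 42/3 = 14 per arm without a baseline FDG scan.
- Without the extra 24: 126 − 42 = 84, or 28 per arm.

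This takes the wave-2 start from section 11.2 and the secondary SAP. The flow chart (Table 3) lists FDG for all seniors without mentioning waves. Even allocation within waves and no dropout are assumed.

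**3. Power by sample size.** Two-sample t test at two-sided 5%, the secondary SAP's level for its other secondary endpoints. The plan gives no FDG effect size, so a range is shown; 0.75 is the primary outcomes' value.

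| True effect (SD) | 28 per arm | 36 per arm | 50 per arm |
|---|---|---|---|
| 0.50 | 45% | 55% | 70% |
| 0.60 | 60% | 71% | 84% |
| 0.75 | 79% | 88% | 96% |

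The first two columns show what the 24 add to FDG. The smallest effect detectable with 80% power falls from 0.76 to 0.67 SD. The last two columns show the head start that Amyvid has if each tracer is analysed in everyone who has it.

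**4. Literal missing = failure on FDG change.** Of 50 per arm, 14 would be imputed: 14/50 = 28%. Both arms receive the same constant in the same proportion, so the arm difference shrinks to 36/50 = 72% of its true value. The spread also changes. If the minimum lies k SDs below the mean, the within-arm variance becomes 0.72 + 0.72 × 0.28 × k².
- k = 2: variance 1.53, SD 1.24, standardised effect 0.72/1.24 = 58% of the true one.
- k = 3: variance 2.53, SD 1.59, standardised effect 0.72/1.59 = 45% of the true one.

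The values of k are assumptions. Wave-1 seniors are scheduled for Amyvid at both visits, so this loss would fall on FDG alone.

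**5. Region.** No calculation applies. Sections 5.1 and 1.2.3.2 point to the anterior cingulate and insula. The FDG regions named in section 10.6.2 are others. Objective 8 names none.

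**The case against.** Much can be said for the plan. FDG is not confined to Alzheimer regions: section 10.6.2 gives both FDG and early-Amyvid maps a whole-brain analysis, the secondary SAP describes voxel-wise PET analysis in general terms, and section 11.3.6 allows values to be extracted from specific regions in any modality. A reader might infer that Objective 8 cannot compare the tracers where the effect is expected. The documents do not support that, because both maps cover the anterior cingulate and insula and Objective 8 assigns no region at all.

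A reader might also infer that FDG was deliberately dropped. That is not shown. The same SAP names FDG in its sample-size text, in Objective 8 and in several exploratory analyses. Its Objective 2 analysis compares imaging measures between the three groups generically. A clerical omission is at least as likely.

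Nor do the documents tie the 24 to Objective 8. They were added for the FDG analysis in general, and they do raise its power, so it would be wrong to say that they deliver nothing.

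Nothing says that sensitivity will be judged by which tracer reaches significance. Under that hypothetical rule, with equal true effects of 0.5 SD and a tracer correlation of 0.5 to 0.8, Amyvid alone would be significant in about 21 to 25% of trials and FDG alone in about 6 to 11%. At 0.75 SD the figures are about 10% and 1 to 2%. With equal numbers some discordance remains by chance, but it is symmetric.

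On missing data, the SAP also defines an available-data strategy and lets the PI choose between its analysis strategies, with ExCom validation. Objective 8 is among the more exploratory objectives.

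What stands is that these provisions permit a sound analysis without specifying one. Whole-brain maps define no paired estimate of relative sensitivity, and the extent of significant voxels also depends on sample size. Leave to extract other regions, or to choose the missing-data strategy, is not pre-specification.

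**Conclusion.** The point holds as a gap in specification, together with one inconsistency between documents. The secondary SAP's radiological list omits an outcome that the protocol and primary SAP include and that its own sample-size section relies on. No FDG endpoint is named in the anterior cingulate or insula. Objective 8 has no common region, population or metric.

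Firm, given the planned wave sizes and a wave-2 start: at most 108 people with FDG against 150 with Amyvid, and 28% of each arm imputed if missing = failure is applied literally, which shrinks the FDG arm difference to 72%. Assumption-dependent: the power differences (15 percentage points at 0.5 SD, 8 at 0.75 SD) and the fall of the standardised effect to 45 to 58%. The documents give no FDG effect size, so the actual distortion cannot be stated.

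The primary outcomes are not affected. This is a cheap improvement that should be made, not a flaw that invalidates the FDG work.

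**What to change.** In the secondary SAP:

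1. Restore change in resting FDG uptake to the radiological outcomes.
2. Add FDG SUVR in the anterior cingulate (meditation versus no intervention) and in the insula (meditation versus English), with the same masks and contrasts as the primary perfusion outcomes. Keep the whole-brain and Alzheimer-region analyses.
3. State that wave-1 seniors, who were not scheduled for baseline FDG, are left out of FDG analyses and are not imputed as failures.
4. For Objective 8, use only participants with both tracers at V1 and V3. Report the difference between the two standardised arm effects with an interval that respects the pairing, for example a bootstrap that resamples participants within arm. State the alpha or confidence level.

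The cost is SAP wording and two region extractions from scans already planned, with no new procedures. The price is precision on the Amyvid side of Objective 8, which would use at most 108 people rather than 150. The primary perfusion analysis keeps everyone.
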